Chronic cephalea and cephalea associated with TMD have benefited from photobiomodulation for pain control. Therapeutic effects of LILT in TMD and headaches include an inflammatory modulator and analgesic effects.^[21–24]^ LILTs have demonstrated the ability to aid in the symptomatic treatment of pain, providing a considerable degree of comfort to patients right after their application. One of the main advantages of LILT is that it is a noninvasive, low-cost pain relief therapy. The use of laser therapy in patients with facial pain showed pain relief within minutes after its application, providing a significant well-being state. It is an auxiliary treatment for pain relief due to the analgesic action of the laser that allows the patient to resume their activities, providing more comfort and a better quality of life.^[21,22,24–26]^

Considering the auxiliary potential effect of photobiomodulation in controlling persistent TTH and TMD-related pain in patients who have been diagnosed with COVID-19, and are recovered from the viral infection, we intend to conduct a clinical trial comparing two modalities of therapeutic laser application: local application and transcutaneous application in the radial artery.

One of the main advantages of auxiliary techniques in pain control is the decrease of the use of drugs for analgesia, avoiding side effects and tolerance caused by them, and promoting an improvement in the individual’s quality of life.

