## 2. Method

This is a pragmatic, randomized, parallel, single-blind clinical trial. The design follows the international recommendations for randomized clinical trials that are displayed in the SPIRIT Statement (Standard Protocol Items: Recommendations for Interventional Trials).

The research follows the regulatory norms established for human subjects research by the Research Ethics Committee of the Nove de Julho University with approval under number 4.673.963 that will periodically monitor the conduct of the study through semiannual reports. This is a low-risk study and symptom relief assessment does not require DMC. The participants will sign the free consent form after clarification, according to resolution 466/12 of the National Health Council. The recruitment procedures, eligibility assessment, and treatment will be carried out at UNINOVE’s Integrated Health Outpatient Clinics.

The selected subject will be individuals from the ages of 18 to 65 years, of both sexes, who have been diagnosed with COVID-19, confirmed by RT-PCR for SARS-CoV-2 already recovered at least 30 days from the infection, and present with orofacial pain will be selected.

Since this is a new scenario in health care and the information on the participants’ conditions is very recent, we chose a convenience sampling design. Considering a prevalence of persistent orofacial pain in infected participants of 11%,^[11]^ with a margin of error of 5%, reliability of 95%, and power of 80%, we intend to recruit, at least, 40 participants.

Participants will be invited to participate in the selection criteria that will follow the routine anamnesis and diagnosis of the International Classification of Headache and orofacial pain questionnaire.

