### 2.7. Research conduct and protocol

The treatment will be carried out in 8 weeks (2 sessions per week) with an average duration of 60 minutes per session. At the end of the 8-week treatment, a new evaluation will be performed after 1 month of follow-up.

After selection, the participants will be randomized into two groups: (G1) photobiomodulation with red and infrared laser with local application on pain points and (G2) photobiomodulation with red laser with transcutaneous application in the radial artery.

The draw for allocation to the groups will be carried out by means of generating number sequences on the electronic platform www.randon.org. The sequence will be kept in a sealed opaque envelope. Only one researcher will have access to the sequencing.

After allocation, the participants will answer the evaluation scales and the blood will be collected for analysis of the initial lactate level (Fig. 1).

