### 2.8. Statistical analysis

The data will be presented descriptively as to the sociodemographic variables and clinical characteristics of the sample. The data of the clinical variables will be analyzed by statistical software SPSS 23.0 for Win. After the normality test, Analysis of variance (ANOVA) followed by Tukey’s test will be applied when necessary and for the treatment results in the study periods, the paired *t* test will be used. If the hypothesis of normality is rejected, the Kruskal–Wallis test will be used followed by Student’s test, and for comparison in the different study periods, the Wilcoxon test will be used. We will take α = 0.05 as the level of statistical significance.

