## 3. Discussion

Pandemic COVID-19 is shown to be a potential factor in the development, worsening, or persistence of TTH and/or orofacial pain.^[5,9,10,12,13]^

Explanatory studies evaluate “if” and “how” the intervention works when applied to participants (efficacy). However, the observed benefits of the interventions may be delimited to a very particular category of participants who met the strict criteria for inclusion or selective exclusion of these patients.^[27]^ When the study intends to evaluate effectiveness, the intervention, already with previously proven effectiveness, should be tested in “real world” conditions.^[26,27]^

This research with a pragmatic trial is justified to respect the features of multimodal treatment of orofacial pain and promote improvement in the quality of life of individuals with TTH and TMD since the literature has already demonstrated the effectiveness of photobiomodulation in explanatory trials.

The aim is to reproduce the conditions found in the clinical routine, since simplified procedures but complex elaboration, derive few or no changes in the clinician’s work routines. The control of variables in the analyses of the results will be done using statistical tests and subgroup evaluations. This pragmatic clinical trial should be seen as complementary to explanatory trials in producing evidence and aiding clinical decision-making.

Persistent symptoms after COVID-19 infection should be treated with care and concern for the patient’s well-being. The results of this study may support clinical choices and decision-making regarding noninvasive and non-pharmacological adjuvants for the control of tension-type headache and TMD-related orofacial pain. It is expected that the tested protocols will be evaluated for their effect on analgesia, compliance to treatment by the patient, and comfort in the application. The results will serve as input for the development of clinical protocols and therapeutic guidelines.

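### Section 2.8 ties treatment results to before-after tests, never says which test compares G1 with G2, and sends non-normal data back to Student's test

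*Protocol article*

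**What the plan says.** The Introduction gives the aim as a comparison: "we intend to conduct a clinical trial comparing two modalities of therapeutic laser application". Section 2 calls the trial randomised and parallel, and section 2.7 confirms two arms: "the participants will be randomized into two groups". Both arms receive laser, and there is no sham or untreated arm.

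Section 2.8 then sets out two branches after a normality test.

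- Normal data: "Analysis of variance (ANOVA) followed by Tukey’s test will be applied when necessary". The next clause reads "for the treatment results in the study periods, the paired" t test.
- Non-normal data: "the Kruskal–Wallis test will be used followed by Student’s test, and for comparison in the different study periods, the Wilcoxon test will be used".

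The threshold follows: "We will take α = 0.05 as the level of statistical significance". Sidedness is not given. No factor (arm, time or both) is named for ANOVA or Kruskal-Wallis. The Abstract lists the same families of test, without a Student step after Kruskal-Wallis, and does not say which one compares the arms.

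**The concern.** A paired t test or a Wilcoxon test across study periods compares participants with themselves. It does not estimate the difference between routes, yet it is the only kind of test that section 2.8 links to treatment results. Entrants are chosen for persistent pain and everyone is treated, so natural course, regression to the mean and placebo response all enter the before-after change. If the arms are then judged by whether each one's change is significant, a chance split can pass for a difference between routes. The Discussion says "The results will serve as input for the development of clinical protocols and therapeutic guidelines", so such a misreading would have consequences.

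The second problem is internal. Once normality is rejected, the plan moves to a rank test and then straight back to Student's test. The two can disagree, and no rule says which counts.

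**Working it through.** Section 2.8 contains no figure to reproduce apart from alpha. The check therefore asks what each reading of the section would produce.

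**Inputs.** Two arms (2.7). At least 40 participants (section 2), taken as 40/2 = 20 per arm; 1:1 allocation is an assumption. Alpha 0.05 (2.8), taken as two-sided. The article gives no SD, effect size or baseline correlation, so these are shown as ranges.

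**1. Separate before-after tests when both arms change equally.** Let p be the chance that one arm's paired t test is significant. The chance that exactly one of the two arms is significant, in either direction, is 2p(1 − p). For a mean change of 0.5 SD of the change, p = 0.565, so 2 × 0.565 × 0.435 = 0.49. Simulation of 100,000 trials per row gave:

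| True change, both arms (SD of change) | p per arm | Exactly one arm significant | Direct between-arm t test on change |
|---|---|---|---|
| 0 | 0.050 | 9.7% | 5.0% |
| 0.2 | 0.136 | 23.6% | 5.0% |
| 0.3 | 0.249 | 37.2% | 5.0% |
| 0.44 | 0.462 | 49.7% | 5.1% |
| 0.5 | 0.565 | 49.3% | 5.0% |
| 0.66 | 0.799 | 32.2% | 5.0% |
| 0.8 | 0.924 | 14.0% | 4.9% |

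The maximum of 2p(1 − p) is 50%, at p = 0.5. A split in one named direction, say G1 significant and G2 not, has half the tabulated chance: about 25% at 0.5 SD.

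**2. ANOVA, Tukey and Kruskal-Wallis with two arms.** On one simulated data set of 20 per arm, ANOVA, the two-sample t test and Tukey all gave p = 0.1614. Kruskal-Wallis and the Mann-Whitney test without continuity correction both gave p = 0.1046. With arm as the factor these are valid two-sample tests, and Tukey adds nothing. If the factor were repeated time points instead, the independence assumption of ordinary ANOVA and Kruskal-Wallis would fail. The text does not say which is meant.

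**3. Kruskal-Wallis followed by Student's t.** From 20,000 simulated trials with lognormal data, 20 per arm:

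| | t rejects | Kruskal-Wallis rejects | Either | Both |
|---|---|---|---|---|
| No effect | 3.7% | 5.1% | 6.5% | 2.3% |
| Log-shift 0.8 | 51% | 67% | – | 47% |

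With no effect, t fails to confirm a significant Kruskal-Wallis result in 1 − 0.02325/0.0513 = 55% of cases. With the shift, the figure is 1 − 0.4736/0.6683 = 29%. Requiring both tests lowers power from 67% to 47%.

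**4. Gain from baseline adjustment.** With 20 per arm, 80% power and the t distribution, the detectable difference in end values is 0.91 SD (0.909 before rounding). Adjusting for a baseline with correlation r multiplies this by √(1 − r²); analysing change scores multiplies it by √(2(1 − r)).

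- r = 0.5: adjusted 0.909 × 0.866 = 0.79; change score 0.909 × 1 = 0.91.
- r = 0.6: adjusted 0.909 × 0.8 = 0.73; change score 0.909 × 0.894 = 0.81.

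**The case against.** The best defence is that section 2.8 twice sets a group procedure beside a paired one, and the paired one is labelled as a comparison over study periods. The natural reading is ANOVA or Kruskal-Wallis between arms, and paired t or Wilcoxon over time. On that reading a valid between-arm test exists. This stands against the inference, which a reader might draw, that the plan cannot deliver a valid between-arm result or uses procedures unsuited to two arms. Step 2 shows that it can, and that Tukey is redundant rather than harmful.

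It is also fair that section 2.8 nowhere says the paired tests will run separately by arm, or that the arms will be ranked by which one reaches significance. The percentages in step 1 are therefore conditional on that use, and the 49% lies near the top of the range.

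The Student step is confined to one sentence and inflates type I error only slightly. Baseline adjustment is a matter of precision, since an unadjusted randomised comparison is valid, and model form is often left to an SAP. The lack of a sham arm fits a stated aim of comparing routes.

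Two things remain. The section attaches treatment results to the paired test and never assigns a test to the comparison that is the trial's aim. And a fuller SAP would not make Student's test after rejected normality consistent with the plan's own condition.

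**Conclusion.** The point holds as a fault of identification plus one internal contradiction. Section 2.8 does not state the between-arm contrast and links treatment results to within-participant tests. If arms were judged by separate before-after tests, the chance of exactly one significant arm despite equal true change would run from about 10% to 50% for changes of 0 to 0.5 SD, falling to 14% at 0.8 SD, against about 5% for a direct test. This assumes 20 per arm, two-sided testing and normally distributed changes.

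The non-normal branch is wrong as written. Under the lognormal example its cost is mainly power and contradictory results; type I error reaches only about 6.5% even if either test counts.

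A reader might go further and conclude that the trial will declare laser effective, or one route superior, without evidence. The article does not say it will draw either conclusion in that way. What can be said is that within-arm change could support neither claim. The gain from baseline adjustment depends on an unknown r and on whether end values or change scores are the alternative.

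**What to change.** Rewrite section 2.8 along these lines:

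- State that the inferential result is the G1-G2 difference with its 95% CI, adjusted for the baseline value. Use ANCOVA at the end of treatment, or a mixed model with arm-by-time for outcomes measured weekly or per session (BPI, VAS, lactate).
- Before fixing the time point, reconcile the treatment duration: the Abstract gives 4 weeks and section 2.7 gives 8. For HIT-6, reconcile the four assessments and the start-and-end schedule, both in section 2.5.
- Replace Kruskal-Wallis plus Student's test with a Mann-Whitney test or rank ANCOVA, and drop Tukey.
- Report within-arm changes descriptively, and say that they are not evidence that laser works or that one route is better.

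The cost is a rewritten paragraph and a little more programming. The measurements needed are already planned, and nothing changes for participants.

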### 2.9. Analysis, data management, and dissemination

The data collected during the research will be stored and organized in the Harvard Dataverse repository (https://dataverse.harvard.edu). The metadata will be published on the site in the repository via the electronic address provided by the platform (DOI).

The data concerning the participants and the research outcomes will remain confidential. Only researchers will have access to this information. Upon completion of the research, the data will be published and disseminated in national and international scientific events and journals.

### 2.10. Patient and public envolviment

The development of this project relied on a multidisciplinary team from Universidade Nove de Julho. The results will be discussed with the study groups involved and will also be disseminated to the participants who requested them and will be published in the newsletters of Universidade Nove de Julho.

## 3. Discussion

Pandemic COVID-19 is shown to be a potential factor in the development, worsening, or persistence of TTH and/or orofacial pain.^[5,9,10,12,13]^

Explanatory studies evaluate “if” and “how” the intervention works when applied to participants (efficacy). However, the observed benefits of the interventions may be delimited to a very particular category of participants who met the strict criteria for inclusion or selective exclusion of these patients.^[27]^ When the study intends to evaluate effectiveness, the intervention, already with previously proven effectiveness, should be tested in “real world” conditions.^[26,27]^

This research with a pragmatic trial is justified to respect the features of multimodal treatment of orofacial pain and promote improvement in the quality of life of individuals with TTH and TMD since the literature has already demonstrated the effectiveness of photobiomodulation in explanatory trials.

The aim is to reproduce the conditions found in the clinical routine, since simplified procedures but complex elaboration, derive few or no changes in the clinician’s work routines. The control of variables in the analyses of the results will be done using statistical tests and subgroup evaluations. This pragmatic clinical trial should be seen as complementary to explanatory trials in producing evidence and aiding clinical decision-making.

Persistent symptoms after COVID-19 infection should be treated with care and concern for the patient’s well-being. The results of this study may support clinical choices and decision-making regarding noninvasive and non-pharmacological adjuvants for the control of tension-type headache and TMD-related orofacial pain. It is expected that the tested protocols will be evaluated for their effect on analgesia, compliance to treatment by the patient, and comfort in the application. The results will serve as input for the development of clinical protocols and therapeutic guidelines.

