### 2.4. Study variables

Sociodemographic information will be collected, such as age, self-reported skin color, education, occupation, weight, height, and practice of physical activity. Besides the sociodemographic information, clinical information will be collected, such as the history of systemic diseases and personal and family history of health problems, treatments performed previously and at the time of the survey, and medications used.

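### Subgroup evaluation is offered as the way to control variables, but it gives no G1–G2 difference adjusted for them; adjusting for the baseline score would, and would gain precision

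*Protocol article*

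**What the plan says.** The Discussion states how other variables will be handled: "The control of variables in the analyses of the results will be done using statistical tests and subgroup evaluations". It names no variable, subgroup, model or interaction test.

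Section 2.8 gives the tests. It says "After the normality test, Analysis of variance (ANOVA) followed by Tukey’s test will be applied when necessary", with a paired t test across study periods. If normality is rejected, it turns to Kruskal–Wallis (with a follow-up Student's test) and Wilcoxon. None of these is described with a covariate.

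Section 2.4 lists many variables that could be used for splitting: age, skin colour, education, occupation, weight, height, physical activity and medical history, and also "treatments performed previously and at the time of the survey, and medications used".

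On design and size, section 2 says "This is a pragmatic, randomized, parallel, single-blind clinical trial" and "we intend to recruit, at least, 40 participants". Section 2.7 adds "After selection, the participants will be randomized into two groups", local application (G1) and radial-artery application (G2). The allocation ratio is not given.

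**The concern.** The trial asks whether two ways of applying the laser differ. To control a variable in that comparison is to estimate the G1–G2 difference while allowing for the variable. A subgroup evaluation answers another question: what the difference is among participants who share one level of the variable. It gives several estimates, each from fewer people, and not one adjusted estimate. A continuous variable such as baseline pain would also have to be cut into categories before it could be used this way.

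Two things are at stake. First, the trial collects baseline pain scores that could sharpen the main comparison, and the stated route does not use them for that. Second, in a trial of this size, results within subgroups can easily differ by chance. The Discussion expects the findings to feed clinical protocols and guidelines, so a chance contrast between subgroups could be taken for a real one.

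**Working it through.** **Inputs from the article.** Total at least 40 and power 80% (section 2); α = 0.05 (section 2.8); two randomised groups (sections 2 and 2.7).

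**Assumptions, not in the article.** Allocation 1:1, so 20 per arm; two-sided test; no dropout; a factor that splits the sample 50:50; standardised difference d from 0.3 to 1.2; baseline–outcome correlation r of 0.3, 0.5 or 0.7.

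**1. The plan's own figure.** Section 2 bases its 40 on a prevalence of 11% and a 5% margin of error at 95% reliability. The usual precision formula gives 1.96² × 0.11 × 0.89 / 0.05² = 150.4, so 151 rather than 40. That is a separate matter and does not support this point. What matters here is that no effect size or SD is given for any outcome, so the stated 80% is not tied to the G1–G2 comparison. It is used below only as a reference level.

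**2. Whole sample.** Power ≈ Φ(d / √(2/n) − 1.96), with n per arm. For 80% at n = 20, d = (1.960 + 0.842) × √(2/20) = 0.886 (0.909 with the t test).

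**3. A 50:50 subgroup.** With n = 10 and d = 0.886: 0.886 / √(2/10) = 1.981, and Φ(1.981 − 1.960) = 0.51. The t test, at d = 0.909, gives 0.49. Over a range of d:

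| d | 20 per arm (normal / t) | 10 per arm (normal / t) | Ratio (normal / t) |
|---|---|---|---|
| 0.3 | 16% / 15% | 10% / 10% | 0.63 / 0.64 |
| 0.5 | 35% / 34% | 20% / 19% | 0.57 / 0.55 |
| 0.65 | 54% / 52% | 31% / 28% | 0.57 / 0.54 |
| 0.8 | 72% / 69% | 43% / 40% | 0.60 / 0.57 |
| 1.0 | 89% / 87% | 61% / 56% | 0.69 / 0.65 |
| 1.2 | 97% / 96% | 77% / 72% | 0.79 / 0.75 |

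The ratio runs from 0.54 to 0.79. It applies to a test inside the subgroup; the whole-sample test keeps its power.

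**4. Validity of the unadjusted comparison.** In 20,000 simulated null trials with 20 per arm and a covariate correlated 0.5 with the outcome, the unadjusted t test had a type I error of 0.050 and a mean bias of 0.000. Chance imbalance does occur: for a binary factor present in half the participants, the between-arm difference has SD √(2 × 0.25 / 20) = 0.158, about 16 percentage points. The test's error rate already allows for it.

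**5. Gain from baseline adjustment.** ANCOVA reduces the residual SD by √(1 − r²). Power becomes Φ(2.802 / √(1 − r²) − 1.960), ignoring the lost degree of freedom:

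- r = 0: 80%
- r = 0.3: 2.802 / 0.954 = 2.937, giving 84%
- r = 0.5: 2.802 / 0.866 = 3.235, giving 90%
- r = 0.7: 2.802 / 0.714 = 3.923, giving 98%

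**The case against.** The strongest reply is that this is one sentence in the Discussion of a condensed article. Covariate lists, model form and subgroup definitions usually sit in an analysis plan, and that is not shown. This stands as far as missing detail goes: the absence of a covariate model is not the finding. The finding is that the article does state a means of controlling variables, and that this means does not do the job.

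The sentence also mentions statistical tests, and section 2.8 does not give the factors in the ANOVA. An ANOVA with a second factor would adjust for that factor, and a Tukey follow-up would make little sense with two groups alone. That reading is possible but not stated. Kruskal–Wallis, the alternative if normality is rejected, has no place for a covariate.

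A reader might infer three stronger things, which the article does not support:

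- **That the main comparison is confounded.** Allocation is randomised, so the unadjusted difference is unbiased and the test holds its 5% level.
- **That the trial's power is halved.** Subgroup analyses leave the whole-sample comparison as it was. The fall applies only within subgroups.
- **That the false-positive rate is inflated by a known amount.** Two independent 5% subgroup tests would give 1 − 0.95² = 9.8%, and more tests would give more. But the article states neither how many subgroups there will be nor that each will be judged by its own p-value.

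**Conclusion.** The point holds as one of method and efficiency. Subgroup evaluation is presented as control of variables, it does not supply an adjusted G1–G2 difference, and no test in section 2.8 is described as supplying one. The main comparison remains valid.

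The cost is precision. Against a reference of 80% power, leaving out baseline adjustment forgoes about 4, 10 or 18 percentage points at r = 0.3, 0.5 or 0.7, and nothing if baseline is unrelated to outcome. Inside a half-sample subgroup, power would be about 50% where the whole sample has 80%. These sizes rest on 1:1 allocation, no dropout, a 50:50 split and the assumed d and r. The conclusion that splitting is not adjusting does not depend on them.

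**What to change.** Replace the Discussion sentence and add wording of this kind to section 2.8: *The G1–G2 difference in each pain outcome at the end of treatment will be estimated, with its 95% confidence interval, from a linear model (ANCOVA) with the baseline value of that outcome as covariate. Subgroup results will be exploratory, shown as estimates with 95% confidence intervals, and judged by the treatment-by-subgroup interaction, not by separate within-subgroup p-values.*

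Three details need care:

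- Pain type may be added as a covariate only with categories that allow for both conditions, because the Abstract admits tension headache, orofacial pain or the two together. A two-level factor would leave some participants unclassified.
- The text should name the reading used as baseline and as outcome. The VAS is taken at the start and end of every session and the BPI weekly (section 2.5).
- The end of treatment must be a single time point. The Abstract gives 4 weeks and section 2.7 gives 8, and the two must be reconciled.

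The cost is small. The pain scales are already answered at the outset (section 2.7), so no new data are needed. With one covariate the residual degrees of freedom go from 40 − 2 = 38 to 40 − 3 = 37, and a few more are used if pain type is added. There is also less scope for subgroup claims. The change should be made before the data are analysed.
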